##### Motivation to exercise according to the self-determination theory

The Behavioral Regulation during Exercise Questionnaire (BREQ-3) [80, 81] comprises 23 items (4 for intrinsic regulation, 4 for integrated regulation, 3 for identified regulation, 4 for introjected regulation, 4 for external regulation and 4 for discouragement) that measure the stages of the self-determination theory with respect to motivation to exercise. Participants will answer each item on a 5-point scale ranging from 0 (not true for me) to 4 (very true for me).

##### Basic psychological needs in exercise

The Basic Psychological Needs in Exercise Scale (BPNES) will be used to measure the basic psychological needs of the participants during exercise. It is a 5-point scale: (1) I don’t agree at all, (2) I agree a little bit, (3) I somewhat agree, (4) I agree a lot, and (5) I completely agree. This scale has previously proven to be a valid instrument for assessing the 3 needs of autonomy, competence, and relatedness in the exercise domain according to the self-determination theory [82, 83].

##### Personality

Personality will be assessed using the Spanish version of the NEO-Five Factor Inventory (NEO-FFI) [84, 85]. This questionnaire measures the Big Five personality factors (*i.e.,* neuroticism, extraversion, openness, conscientiousness, and agreeableness) through 60 items on a 5-point Likert scale: (1) I strongly disagree, (2) disagree a little, (3) neither agree nor disagree, (4) agree a little and (5) strongly agree [86].

##### Confounding variables

Confounding variables will be assessed in baseline using an ad-hoc demographic questionnaire, including the following: (1) sex (*i.e.,* male or female); (2) birth date; (3) marital status (*i.e.,* single, married, widowed, divorced, or domestic partner); (4) living situation (*i.e.*, living alone, with partner or with family); (5) educational level (*i.e.,* elementary, high school or university); (6) socioeconomic level (*i.e.,* < 14.000, 14.000–30.000 or > 30.000 euros per year); (7) race (*i.e.,* caucasian, african-american, asian, native-american or other); (8) smoking status (*i.e.,* non-smoker, ex-smoker [not having smoked in the last 6–12 months] or current smoker); (9) self-reported falls in the last year (*i.e.,* none, one or two); (10) number of diseases (*i.e.,* none, cardiovascular disease, cerebrovascular disease, high blood pressure, anxiety and/or depression, diabetes mellitus, high cholesterol, osteoporosis, renal disease, liver disease, cirrhosis, hepatic insufficiency, osteoarthrosis, rheumatoid arthritis, hyperthyroidism, hypothyroidism or other); (11) alcohol consumption (*i.e.,* never, once a month or less, 2–4 times a month, 2–3 times a week, 4 or more times a week) and (12) body mass index. These data will be used for descriptive statistics and as covariates for the analyses.

### Data collection and management

Outcomes will be assessed at baseline, mid-intervention (*i.e.,* week 13), at the end of the intervention (*i.e.,* week 25), and 24 weeks later (*i.e.,* week 49). At each measurement point –except for the mid-intervention measurement, which will only involve 1 session– participants must perform all assessments in 5 different days interspersed by at least 48 h and a maximum of 1 week. Trained assessors will conduct all assessments. A detailed scheme of the outcomes assessed in this study is shown in Figs. 1 and 3.

**Fig. 3 Fig3:**
[figure not shown]
Assessment protocol. BPNES: Basic Psychological Needs in Exercise Scale; BREQ-3: Behavioral Regulation during Exercise Questionnaire; DSST: Digit Symbol Substitution Test; EBBS: Exercise Benefits/Barriers Scale; EQ-5D: EuroQoL-5 dimensions quality of life questionnaire; IPAQ: International Physical Activity Questionnaire; MoCA: Montreal Cognitive Assessment; NEO-FFI: NEO-Five Factor Inventory questionnaire; PSQI: Pittsburgh Sleep Quality Questionnaire; TMT A-B: Trail-Making Test Part A and B

Participation in the project is voluntary, so participants may withdraw from the study at any time. Data collected from them are retained confidentially by the project team and included in the analyses. Personal information about potential and enrolled participants will be collected, shared, and maintained with codes to protect confidentiality throughout the trial.

The paper data will be stored in coded (re-identifiable) format in a locked filing system at the University of Castilla-La Mancha. The electronic data will be encrypted (re-identifiable) and stored in private computer systems. Only the research team will have access to the trial data. The databases will be prepared by two independent evaluators with double data entry.

### Statistical analysis

Data will be preferentially presented as mean ± standard deviation or as proportions for continuous and categorical variables, respectively. Data normality will be assessed by the Kolmogorov–Smirnov test and will be log-transformed in case of non-normal distribution. Baseline differences will be assessed through a one-way ANOVA. A two-way mixed ANCOVA (group [*i.e.*, CON, SUP, SUP + , UNSUP, and UNSUP +] x time [*i.e.,* baseline, mid, post-intervention, and follow-up assessments]) will be performed, adjusting for baseline values as well as for any other sociodemographic/descriptive variables that may differ between groups (*e.g.,* age, sex). Subsequent post-hoc tests will be conducted to determine which groups significantly differ. Effect sizes will be calculated to assess the magnitude of the differences [87]. Falls and fall-related injuries will be presented as rates/person (ITT analysis) and rates/person/year (± 30 days; PP analysis), and as numbers. Adverse events and dropouts will be compared between groups through Chi-squared tests. Differences in adherence rates will be analyzed using an ANOVA test. Correlation analyses will be used to assess associations between motivators, barriers, and adherence to exercise sessions. Whenever possible, statistical analyses will be performed on an intention-to-treat (ITT) basis (including all randomized participants). The potential effects of missing values and dropouts will also be explored using multiple imputation and sensitivity analyses [88]. As recommended, a complementary per protocol (PP) analysis will be performed (*i.e.,* including only those participants with valid data for baseline and post-intervention assessments and an adherence to exercise program of at least 80%) [89]. SPSS version 24.0 (IBM Corp., Armonk, NY) will be used for statistical analysis, and the significance level will be set at p ≤ 0.05 for all tests.

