**Methods:**

Participants (*n* = 120, aged 60–75 years) will be randomly allocated into five groups: 1-Control (CON), 2-Supervised exercise without motivational intervention (SUP), 3- Supervised exercise with motivational intervention (SUP +), 4- Unsupervised exercise without motivational intervention (UNSUP) and 5- Unsupervised exercise with motivational intervention (UNSUP +). Over 24 weeks, all exercise groups will participate in a multicomponent exercise program three times/week (performed in group classes at a center for SUP and SUP + , or home without supervision but with the help of a mobile app for UNSUP and UNSUP +), while the CON group will maintain their usual lifestyle. The motivational intervention (for SUP + and UNSUP + groups) will be based on the self-determination theory, including strategies such as phone calls, interactive workshops, motivational messages, informative infographics and videos. Primary outcomes will include safety, adherence, costs, and lower-body muscular function using a leg press machine. Secondary outcomes will include upper-body muscular function, physical and cardiorespiratory function, blood pressure and heart rate, body composition, health-related quality of life, cognitive performance, anxiety, depression, physical activity levels, sleep and sedentarism, biochemical markers, motivators and barriers to exercise. Assessments will be conducted at baseline, mid-intervention (*i.e.,* week 13), at the end of the intervention (*i.e.,* week 25), and 24 weeks later (*i.e.,* week 49).

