### Trial groups

All participants allocated to exercise intervention groups will complete a 24-week multicomponent exercise program consisting mostly of resistance exercises (3 sessions per week; 60 min per session). The exercise program will be reported following the Consensus on Exercise Reporting Template (CERT) [38] (see Supplementary Table 2). After completing the baseline assessment, participants will be randomly allocated to the 5 study groups. After randomization and irrespective of intervention group allocation, a member research team member will inform the participant about the intervention and assessment plan.

The exercise program for all intervention groups will be divided into 3 difficulty levels, increasing every 8 weeks. Each will include 3 sessions comprising of warm-up, balance, resistance, aerobic, and flexibility exercises (Tables 1 and 2). Further information about the training variables is available in Supplementary Table 3.

**Table 1 Tab1:** Supervised exercise program

	**Session nº**	**Exercise nº**	**Intensity report**	**LEVEL 1**	**LEVEL 2**	**LEVEL 3**	**Type**
WARM-UP	1, 2 & 3	1	-	Seated ankle circumduction			Joint mobility
		2	-	Knee flexo-extension			
		3	-	Hip circumduction			
		4	-	Forward–backward shoulder circumduction			
		5	-	Wrist circumduction			
		6	-	Neck mobility			
		7	-	Diagonal foot touches	Foot touches forward, to the side and back with hands on the waist	Foot touches forward, to the side and back with arms in cross position	Balance
		8	-	Heel lifts	One leg balance	One leg balance with arms in cross position	
		9	-	Lateral movement without impact	Lateral movement with impact	Rope skipping	Soft cardio
		10	-	´V´ front	Knee-elbow	Low skipping	
MAIN ACTIVITY	1	1	-	One leg balance with arms in cross position	One leg balance with leg abduction	One leg balance with shoulder flexion	Balance
		2	RIR	Machine chest press	Cable crossover	Dumbbell chest press	UB push (pectoral, triceps)
		3	RIR	Box squat	Goblet squat	Jump squat	LB (quadriceps, gluteus)
		4	RIR	Pulley shoulder flys	Alternating dumbbells shoulder flys	Simultaneous dumbbells shoulder flys	UB pull (trapezius, deltoid)
		5	RIR	Assisted TRX lunge	Lunge	Weighted lunge	LB (quadriceps, gluteus)
		6	RPE	Front plank with shoulder touches	Front plank with knees	Front plank	Core
		7	RIR	Seated rowing machine	Standing cable row (medium height)	Unilateral dumbbell row	UB pull (dorsal)
		8	RIR	Knee-banded seated hip abduction	Monster walk	Clamshell	LB (gluteus)

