##### Adherence to the program

Adherence to the program will be calculated as a ratio between the sessions completed from those initially prescribed ([sessions completed/total sessions expected] × 100), where 0% indicates total non-adherence and 100% indicates full adherence [40]. The sports scientist will record adherence to the exercise program in the SUP and SUP + groups [41], while in the UNSUP and UNSUP + groups, it will be automatically registered through the mobile app [42].

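### The log-transform rule cannot be applied to a 0% value of adherence, a primary outcome: if it is triggered, observed complete non-adherers are lost from the analysis

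*Protocol article*

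**What the plan says.** The abstract lists the primary outcomes: "Primary outcomes will include safety, adherence, costs, and lower-body muscular function using a leg press machine". The section Adherence to the program defines adherence as sessions completed over sessions expected, times 100, "where 0% indicates total non-adherence and 100% indicates full adherence". Zero is therefore a defined value of the outcome, not a missing one.

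The Statistical analysis section sets one general rule for distributional shape: data are checked by the Kolmogorov–Smirnov "test and will be log-transformed in case of non-normal distribution". It names no outcome to which the rule does not apply, no offset and no alternative. The same section gives the test for this outcome: "Differences in adherence rates will be analyzed using an ANOVA test". On the analysis population it says: "Whenever possible, statistical analyses will be performed on an intention-to-treat (ITT) basis (including all randomized participants").

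**The concern.** A log transformation needs strictly positive values. Software returns a missing value for the log of 0, and an ANOVA on the logged variable then omits that participant. Those omitted are selected on the outcome itself: they are exactly the people who did no sessions. Because their value was observed, the multiple imputation planned for missing data and dropouts is not meant for them.

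The effect of supervision and motivation on adherence is part of the trial's stated main goal. If complete non-adherence is more frequent without supervision, losing those participants makes the unsupervised arms look more adherent than they were and shrinks the contrast. A second problem is that a log is the wrong tool for the shape of a ratio bounded at 0 and 100%.

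**Working it through.** **Inputs from the protocol.** Adherence runs from 0 to 100%. The exercise groups "will complete a 24-week multicomponent exercise program consisting mostly of resistance exercises (3 sessions per week; 60 min per session"), so 24 × 3 = 72 sessions are expected and the smallest non-zero value is 100/72 = 1.39%. Enrolment is 120 in five groups. If allocation is equal (an assumption, as the ratio is not stated), that is 24 per arm, 48 in the two unsupervised arms and 96 in the four exercise arms. The protocol gives no expected adherence distribution, so every distribution below is assumed.

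**1. What the rule does to a zero.** ln(100) = 4.61, ln(1.39) = 0.33, and ln(0) is undefined. A participant with one session stays in; a participant with none does not.

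**2. Chance of meeting a zero.** Among the 48 unsupervised participants, P(at least one zero) = 1 − (1 − p)^48. For assumed p = 2%, 5% and 10% this is 62%, 91% and 99%.

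**3. Chance that the rule is triggered.** Take adherence with mean 73% (beta-binomial over 72 sessions, Beta(4, 1.5)) and n = 96. The Lilliefors form of the Kolmogorov–Smirnov test rejects normality in 77% of samples with no added zeros, 97% with 5% zeros and over 99% with 10%. The protocol does not say whether the test is pooled or by group. In the step 5 example, with an arm of 24, the Lilliefors form rejects in about 65% of samples. The uncorrected form rejects in about 13% (supervised) and 3% (unsupervised).

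**4. Bias in one arm.** If the non-zero adherers in an arm of 24 average 72.7% and z participants have 0%, the true arm mean is 72.7 × (24 − z)/24. The mean after the log has dropped the zeros stays at 72.7%.

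| z | Mean, zeros kept | Mean, zeros lost | Upward bias (points) |
|---|---|---|---|
| 0 | 72.7 | 72.7 | 0 |
| 1 | 69.7 | 72.7 | 3.0 |
| 2 | 66.6 | 72.7 | 6.1 |
| 3 | 63.6 | 72.7 | 9.1 |
| 5 | 57.5 | 72.7 | 15.1 |

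**5. Effect on the contrast (assumed example).** Supervised: 3% zeros, the rest Beta(8, 1.5) with mean 8/9.5 = 84.2%. Unsupervised: 15% zeros, the rest Beta(5, 2.2) with mean 5/7.2 = 69.4%.

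- Zeros kept: 0.97 × 84.2 = 81.7 and 0.85 × 69.4 = 59.0, a difference of 22.7 points.
- Zeros lost: 84.2 − 69.4 = 14.8 points.
- Loss: (22.7 − 14.8)/22.7 = 35%.

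A log-scale ANOVA compares geometric means. With zeros lost these are about 83.2 and 67.0, a ratio of 1.24, against 81.7/59.0 = 1.38 for the means of everyone.

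**6. Effect on shape.** Skewness in assumed beta-binomial distributions over 72 sessions, raw and after logging the non-zero values:

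| Mean adherence | Raw | Logged |
|---|---|---|
| 80% | −0.84 | −1.51 |
| 73% | −0.69 | −1.77 |
| 67% | −0.57 | −2.08 |
| 50% | 0.00 | about −1.5 |
| 33% | +0.56 | −1.01 |
| 21% | +1.07 | −0.60 |

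At means of 50% or more the log creates or worsens left skew; at low means it turns right skew into left skew. In the 73% case, after logging with zeros dropped, normality is still rejected in over 98% of samples.

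**7. Does an offset rescue it?** In the step 5 example log(x+1) keeps the zeros, but skewness becomes about −5.2 (supervised) and −1.8 to −1.9 (unsupervised). The back-transformed means are about 73 and 35, against true means of 81.7 and 59.0. The zeros now dominate the estimate.

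**The case against.** The strongest reply has several parts.

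- **Scope.** The adherence sentence stands alone and does not mention transformation, and a fuller analysis plan may set an offset. This is fair as a possibility. But the article states a general rule for data without exception, and the obvious offset also fails.
- **Conditions.** The loss needs a rejected normality test and at least one 0%. Neither is certain, and by-group testing with the uncorrected test would rarely reject. This stands, and the point is conditional for that reason.
- **Shape.** A reader might infer that adherence must pile up near 100% and that the log always worsens a left skew. The documents do not support this: the Background says that adherence to unsupervised programmes is usually low. With low adherence the raw skew may be to the right, and the log overshoots instead.
- **Weight of the zeros.** A reader might infer that zero-session participants carry most of the supervised–unsupervised contrast. In the example they carry about a third.
- **Power.** In the same example, with 48 v 48, the comparison has about 99% power on either scale. The harm is to the estimate and the analysis population, not to power.
- **Intention to treat.** The ITT sentence is qualified, so losing zeros is in tension with the stated aim and not a flat contradiction. That is correct. However, keeping these participants is plainly possible, so the qualifier gives no reason to lose them.
- **Reach.** A reader might go on to demand removal of the normality rule for every outcome. The defect shown here concerns outcomes that can be 0, and goes no further.

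**Conclusion.** The point holds in conditional form. As written, the rule cannot be carried out on a 0% value of a primary outcome. If it is triggered and any zeros occur, observed complete non-adherers are lost and arm means are biased upward. Those conclusions follow from the text and need no assumed figure.

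The size does rest on assumptions. It is about 3 points per lost participant in an arm of 24 whose other members average 73%. In the 3% v 15% example the contrast falls by about a third, from 23 to 15 points. It is nil without zeros. That the log fits this outcome poorly holds across all the assumed distributions tried, from mean 21% to 80%, though the direction of the raw skew is unknown. The matter should be corrected before the analysis.

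**What to change.** State in the Statistical analysis section that adherence is exempt from the log-transform rule. Analyse it in all participants randomised to the four exercise arms, with zeros kept, in one of two ways:

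- on the 0–100% scale, comparing means with robust or bootstrap confidence intervals; or
- as sessions completed out of 72, with a binomial or fractional logit model and robust standard errors.

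Both can be done in the software already named. Add that the log will not be applied to other outcomes that can be 0, such as the 15-item depression score (a secondary outcome). The per-protocol criterion ("an adherence to exercise program of at least 80"%) is already on the percentage scale and needs no change.

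The cost is a change of wording and slightly more analysis work. No data collection or sample size is affected.

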### Sample size

The sample size was determined by a priori power analysis using G ∗ Power 3.1.9.4 software. Input parameters were entered considering repeated measures ANOVA (group by time interaction), setting the probability of α error at 0.05, 1-β = 0.80, and 5 groups. The standardized mean difference used for calculations was 0.43, based on the effect of home-based exercise on lower-body muscle power in older adults reported in a previous meta-analysis [19]. The model indicated a total sample size of 100 individuals, and considering a dropout rate of 20%, we finally decided to enroll 120 participants.

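### Baseline is both a level of the time factor and a covariate in the same mixed ANCOVA, which shrinks the time-averaged group estimate to 3/4 and leaves the tested contrast unclear

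*Protocol article*

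**What the plan says.** The protocol article, Statistical analysis, names one model for the repeated outcomes: "A two-way mixed ANCOVA (group [*i.e.*, CON, SUP, SUP + , UNSUP, and UNSUP" +]) crossed with time. The time factor and the adjustment stand in the same sentence: "baseline, mid, post-intervention, and follow-up assessments]) will be performed, adjusting for baseline values". The covariate list is the baseline value and more: "adjusting for baseline values as well as for any other sociodemographic/descriptive variables that may differ between groups". Nothing elsewhere limits the time factor to post-baseline visits.

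The section then announces post-hoc comparisons between groups and effect sizes. It names no visit, no model term and no error variance for them. The software is given ("SPSS version 24.0 (IBM Corp., Armonk, NY) will be used for statistical analysis") but not the procedure, and "the significance level will be set at p ≤ 0.05 for all tests".

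The Sample size section points to one term, as the calculation was for "repeated measures ANOVA (group by time interaction), setting the probability of α error at 0.05, 1-β = 0.80, and 5 groups". The section on data collection and management confines the mid-intervention visit to a single session, so some outcomes may have three time levels instead of four.

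**The concern.** A variable regressed on itself leaves nothing to explain. Once the baseline value is a covariate, the baseline level carries no information about group, yet it still counts as one of the levels over which the model averages and pools.

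Two results can go wrong:

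- An adjusted group difference averaged over time includes a built-in zero, so it understates the post-baseline difference.
- An error variance pooled over time includes a visit with no variance, so a test at week 25 that uses it is too liberal.

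This is the stated model for the continuous outcomes measured over time, including the primary outcome of lower-body muscular function. The article does not say which term answers the question, so the analyst could report a harmless quantity or an affected one and comply with the text either way.

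**Working it through.** The article states no figure for this point, so there is none to reproduce. The sample size of 100 (120 enrolled) does not enter the argument.

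**Inputs.** From the article: five groups, four time levels with baseline first, baseline as covariate, alpha 0.05, and a standardised difference of 0.43 (Sample size). Assumed: visit-specific covariate slopes, equal allocation (24 per group), complete data, the same effect in all four exercise groups, and compound symmetry with correlation 0.5, 0.7 or 0.85. Correlation 0.8 with AR(1) decay was added for the type I error check.

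**1. Baseline level.** Fitting the planned model by least squares gives a largest absolute baseline residual of 2e-16, and an adjusted baseline difference from control of 0 in every exercise group. With one common slope for all visits the baseline residual is small but not zero (SD 0.12 to 0.31).

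**2. Time-averaged estimate.** Let b be baseline and M the mean of the three post-baseline visits. The four-level mean is (b + 3M)/4. After adjustment for b, its group coefficient is 3/4 of that for M. In one simulated data set the first exercise group differed from control by 0, 0.7827, 0.4896 and 0.0957:

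- post-baseline average: (0.7827 + 0.4896 + 0.0957)/3 = 0.456
- four-level average: (0 + 0.7827 + 0.4896 + 0.0957)/4 = 0.342
- ratio: 0.342/0.456 = 0.75

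Over 2,000 simulated trials per correlation with a constant true effect of 0.43, the mean estimate was 0.43 with post-baseline levels only and 0.32 to 0.325 with baseline as a level. The ratio is also 0.75 with a common slope. With three time levels it is 2/3.

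**3. Test of that estimate.** The residual of (b + 3M)/4 is also 3/4 of the residual of M, so the standard error shrinks by the same factor. In the example F = 3.884 and p = 0.0054 both ways. Power was 0.63, 0.76 and 0.95 at the three correlations, both ways.

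**4. Single visits and interaction.** With visit-specific slopes, the differences at weeks 13, 25 and 49 are the same whether or not baseline is also a level. For the interaction, under a constant effect of 0.43:

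| Model | Power at 0.5 | 0.7 | 0.85 |
|---|---|---|---|
| Baseline as level and covariate | 0.29 | 0.49 | 0.82 |
| Baseline as level only | 0.26 | 0.44 | 0.79 |
| Baseline as covariate only | 0.06 | 0.05 | 0.05 |

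In the planned model its type I error stayed at 0.04 to 0.06. The last row shows that, without the baseline level, group by time no longer detects a sustained constant effect.

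**5. Post-hoc tests at one visit.** If the three post-baseline residual variances are equal to s², pooling over four levels gives (0 + 3s²)/4 = 0.75s². The standard error is then too small by sqrt(0.75) = 0.87. A nominal 5% test rejects when |z| > 1.96 × 0.866 = 1.70, which has probability about 0.09.

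Under AR(1) 0.8 the residual variances are 1 − 0.8² = 0.36, 1 − 0.8⁴ = 0.59 and 1 − 0.8⁶ = 0.74. Their four-level mean is 1.69/4 = 0.42, against 0.59 at week 25. The cut-off is 1.96 × sqrt(0.42/0.59) = 1.66, giving about 0.10.

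Simulation (4,000 replicates, N about 100) gave 0.08 to 0.10 with error pooled over four levels, and 0.047 to 0.060 with week-25 error. Error pooled over post-baseline visits only also stays near 5%. Under AR(1) the cut-off is 1.96 × sqrt(0.563/0.590) = 1.91, or about 0.056.

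**The case against.** The strongest reply is that little of what the trial will report need be affected. The trial was sized on group by time, which the dual role does not dilute. Adjusted differences at a visit do not change, and the main-effect test is identical. An effect size derived from F, such as partial eta squared, does not change either. The type I inflation needs a pooled error term that the article never specifies, and post-hoc detail may sit in an analysis plan that is not shown. All of this stands, and it limits the point. It does not remove the contradiction, which is in the text itself and not in an omitted detail.

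Three stronger readings are tempting, and the document supports none of them:

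- A reader might infer that group effects and effect sizes in general come out a quarter too small. Only the time-averaged difference does, together with any standardised difference built from it and an outcome SD. The article does not name that as its estimate or say which effect size it will use.
- A reader might infer that the post-hoc tests are too liberal. That holds only under four-level pooling.
- A reader might infer that someone missing week 49 drops out of the week-25 comparison, against the intention-to-treat aim. The article never calls its main model complete-case. It says that, whenever possible, "statistical analyses will be performed on an intention-to-treat (ITT) basis (including all randomized participants"), and it adds multiple imputation and sensitivity analyses. That issue is also separate from the dual role of baseline, since a four-level ANOVA without the covariate would raise it too.

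**Conclusion.** The specification is wrong as written, because baseline cannot usefully be a response and its own covariate in one ANCOVA. The certain consequence is narrow: a group difference averaged over the time levels is 3/4 of the post-baseline average (2/3 with three levels), with its test unchanged. The conditional consequence is a type I error of about 8-10% for tests at one visit, if their error is pooled over all four levels.

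The exact zero at baseline rests on visit-specific slopes, which the article does not state. The 3/4 ratio holds with a common slope as well. The simulated power and type I figures rest on the assumed correlations, equal allocation and complete data. What makes this worth correcting is that no target term is named, so both affected quantities remain open to the analyst.

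**What to change.** Give baseline one role and name the tested term, in either of two ways:

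- **(a) Baseline as covariate.** Use weeks 13, 25 and 49 as responses (weeks 25 and 49 where there is no mid-intervention measurement) in a linear mixed model with group, visit, group by visit, baseline and baseline by visit. Keep every participant with at least one post-baseline value. Name the group contrast at week 25 as the target.
- **(b) Baseline as response.** Keep it as a time level and drop it as a covariate; group means at baseline may be constrained equal. Test group by time or the week-25 contrast.

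Do not remove the baseline level and then still rely on the group-by-time test, because power for a sustained constant effect falls to about 5%. State that tests at a visit use that visit's error, or error pooled over post-baseline visits only.

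The cost is a few sentences, settled before unblinded analysis. SPSS MIXED fits model (a), and no new data are needed.

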### Randomization and blinding

The randomization will be performed by a researcher not involved in the study. The allocation sequence will be determined by a computer-generated list (http://www.randomizer.org/). If a couple living in the same house participates, both will be randomized into the same group [37]. Blinding of the intervention is impossible for participants and therapists administering the intervention given its nature (*i.e*., exercise training). During the intervention, subjects will not be told about the existence of groups with and without motivational strategies. Statisticians and assessors in charge of outcome assessments will be blinded to participants’ allocation.

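### Chance baseline imbalance decides which covariates, beyond the outcome's own baseline value, enter the group-by-time ANCOVA

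*Protocol article*

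**What the plan says.** Two sections of the protocol article bear on covariates.

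- **Statistical analysis.** "Baseline differences will be assessed through a one-way ANOVA". The next sentence sets out a two-way mixed ANCOVA with five groups and four assessments, "adjusting for baseline values as well as for any other sociodemographic/descriptive variables that may differ between groups". Age and sex follow in brackets as examples. The section ends by stating that "the significance level will be set at p ≤ 0.05 for all tests".
- **Confounding variables** (under Outcome measures). "Confounding variables will be assessed in baseline using an ad-hoc demographic questionnaire, including the following" introduces a numbered list of 12 items, from sex to "and (12) body mass index". The section closes: "These data will be used for descriptive statistics and as covariates for the analyses". No condition on group differences is attached.

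On allocation, Randomization and blinding states: "The allocation sequence will be determined by a computer-generated list". It mentions no stratification factor that would dictate a covariate. Neither covariate statement is said to take precedence, and no fixed covariate list is given.

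**The concern.** When allocation is random, a baseline difference between groups is a chance event. Its size says nothing about whether the variable predicts the outcome, and prediction is what makes adjustment worthwhile. A rule driven by imbalance can go wrong in two ways: it admits variables unrelated to the outcome because they happened to differ, and it omits likely predictors of leg-press force and power, such as age and sex, because they happened to be balanced.

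The adjusted model for a primary outcome is also not known until the baseline data have been examined. No threshold is tied to the rule and the candidate list is open-ended, so two analysts following the text could fit different models. At stake are precision in a five-group trial of 120 people and the assurance that the reported model was not chosen from several.

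**Working it through.** The documents give no figure for this point, so there is nothing to reproduce. The check compares the two statements and then sizes the consequence under stated assumptions.

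**Inputs from the article**
- 12 candidate variables (Confounding variables).
- Significance level 0.05 for all tests (Statistical analysis).
- 120 to be enrolled, 20% dropout (Sample size), so 120 × 0.8 = 96 expected completers.

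**Assumptions not in the article**
- Selection means p ≤ 0.05 on a valid baseline test.
- The 12 variables are independent.
- Categorical and ordinal items are fully dummy-coded, birth date enters as age, and diseases enter as a count.

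**Reading 1: select on baseline difference**
- Expected number selected by chance: 12 × 0.05 = 0.6.
- Probability that none is selected: 0.95^12 = 0.54.
- Probability of at least one: 1 − 0.95^12 = 0.46.
- Probability of two or more: 0.118 (binomial, 12 trials, 0.05).
- Probability that any one named variable, such as age, is left out: 1 − 0.05 = 0.95, however prognostic it is.

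**Reading 2: enter all 12**

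Parameters as coded: sex 1, age 1, marital status 4, living situation 2, education 2, income 2, race 4, smoking 2, falls 2, disease count 1, alcohol 4, BMI 1. The sum is 26. That leaves 120 / 26 = 4.6 randomised participants per parameter, or 96 / 26 = 3.7 completers, before the group, time and baseline terms are counted.

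The most likely single result under Reading 1 is therefore a model with none of the 12 (54%), while Reading 2 has all of them.

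**Effect on the test**

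A simulation under no group effect compared the two readings, with 4,000 runs per setting. It used five equal groups, N = 100 or 120, one post-baseline outcome, and 12 independent normal covariates assumed to explain 0, 30 or 50% of outcome variance.
- Type I error when selecting on p ≤ 0.05: 0.039 to 0.047.
- Type I error when adjusting for all 12: 0.044 to 0.052.
- The two readings gave different significance decisions in about 2.5 to 3% of trials when covariates were not prognostic, and in about 5 to 6% when they explained 30 to 50% of variance.

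Selection did not inflate type I error and became somewhat conservative when the covariates mattered. The simulation has a single time point and no baseline-outcome term, so it indicates direction and rough size only.

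**The case against.** Several objections have force.

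- **The two sections need not contradict each other.** The Confounding variables list can be read as a pool of candidates from which the analysis section draws. That is a fair reading, so this is a misalignment to clear up rather than a firm contradiction. It leaves the dependence on observed imbalance untouched.
- **The link to p ≤ 0.05 is inferred.** The ANOVA sentence stands just before the covariate sentence, but the article never says that its p-value selects covariates. Items such as marital status and living situation are also plainly related. The 0.6 and 46% are therefore conditional. If there is no threshold, the model is even less defined.
- **ANOVA on categorical items.** A reader might infer that one-way ANOVA will be run on marital status or smoking. No sentence says so; the article may simply not name the test for categorical variables.
- **Different models for different outcomes.** A reader might also infer this. Whether groups differ in age or sex does not depend on the outcome analysed, so within one analysis set the extra covariates would be the same throughout.
- **Protections already in place.** The outcome's baseline value is always adjusted for, and the article gives no figure for how much age and sex would add to it. Statisticians are to be blinded to allocation, which limits selective adjustment. Neither protection fixes the model in advance.

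Leaving detail to a separate analysis plan is no answer here, because the article does state a rule; the fault lies in the rule.

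**Conclusion.** The point holds in a limited form. The stated rule lets chance imbalance choose the additional ANCOVA covariates, so the model for lower-body muscular function and the continuous secondary outcomes is not fixed in advance, and adjustment is not directed at prognostic variables.

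The size is moderate: 0.6 covariates selected by chance on average and a 46% chance of at least one, given a 0.05 screen on 12 independent variables. The alternative reading costs about 26 parameters under full dummy coding.

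Two stronger conclusions are not supported. One is that false positives are inflated: applied mechanically, the rule gave type I error at or below 0.05. The other is that all primary results are affected. Adherence is compared by ANOVA and adverse events by Chi-squared tests, neither with stated covariates, and the adjustment of cost differences is not tied to this rule. The trial remains interpretable, but the rule should be changed.

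**What to change.** - **Statistical analysis section.** Remove observed baseline difference as the criterion for adjustment. Prespecify, before unblinded analysis, one short covariate set for all ANCOVA outcomes: the outcome's baseline value plus age and sex. The latter two are the protocol's own examples. Adherence has no baseline value, so that term does not apply to it.
- **Baseline characteristics.** Present them descriptively.
- **Confounding variables section.** Change the last sentence so that the remaining listed variables are descriptive, or are used only in a sensitivity analysis labelled as such.

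The article does not show which of the 12 variables are most prognostic. If the investigators have grounds for a different short set, naming it in advance serves the same purpose.

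The cost is a rewording in two sections and a few degrees of freedom. No new data are needed: the variables are already planned for collection, although recruitment was still open when the article was written.
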